**4. Trial Procedures**

- An information-sharing meeting will be held on each collection route, gathering all the heads of households to: explain the terms of the study and the targets to achieve in terms of milk collection; perform the intervention lottery to define the treatment and control groups; distribute the explanatory note of the study and the information sheet on anemia (in French and Fulani); and distribute a form indicating willingness to participate in the study (to be brought, signed, to a second meeting 10 days later)
- An awareness-raising campaign will be implemented in the study zone by the Cellule de Lutte contre la Malnutrition (Unit for the Fight against Malnutrition; CLM) in January 2013, through community representatives of ASBEF in villages and through radio commercials, in order to inform mothers on good feeding practices and explain the problems of anemia. This campaign will take place in the study zone for 6 months.
- A first household survey will take place in January 2013, to gather baseline data through the form of a household questionnaire (household composition, herding/cow data, socio-economic data, household consumption etc.); anthropometric data; and hemoglobin measures of children 6 months to 5 years old and their mothers, using HemoCue®.

- A distribution phase of incentives (fortified Thiakry) for 6 months, from January 2013 to July 2013.
- A second phase of data collection in July 2013, through household questionnaire and measurement of hemoglobin levels as during the baseline data collection.
- A third phase of data collection in January 2014, through household questionnaire and measurement of hemoglobin levels.

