# 4. Location of the study

LDB is located in the area of Richard Toll, along the Senegal River Delta in the administrative department of Dagana. Collection routes are located in the Dieri and in the Walo (flood zone near the river, where rice is commonly grown). The herding in the Walo is of a more sedentary/agro-pastoral nature whereas the herding in the Dieri is generally pastoral with transhumance (Parisse, 2011).

[figure not shown]

*Figure 1: Collection routes around Richard Toll, Senegal*

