# 8. Conditions of the lottery

The two groups will be chosen by lottery at the first information-sharing meeting. The draw will define the households receiving free fortified Thiakry for all children aged 2 to 5 years within their household (treatment group) and the households not receiving fortified Thiakry during the study (control group), who will receive in kind compensation at the end of the study as thanks for their participation.

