**10.3.** **Malaria, schistosomiasis, helminths**

As anemia often has multifactorial causes, the WHO recommends an integrated approach to fight against anemia (WHO/UNICEF, 2004). To assess the impact of distributing fortified Thiakry on anemia in the study area, it is necessary to take into account the risk of infection through malaria and helminth infections such as schistosomiasis, which may vary from one zone to the other (Staubli, 2001).

Malaria in Senegal is seasonal, with a higher transmission in the south than in the north and higher levels during the rainy season than during the dry season. In northern Senegal, despite a fairly desert-like environment, the presence of flooding rivers during the rainy season, as well as irrigation practices and seasonal migration, contribute to the transmission of the parasite. However, the transmission remains very low in the area of Richard Toll, averaging 1.2 cases per 1000 inhabitants (Diop, 2012). According to the 2008-2009 DHS data, the national prevalence of malaria at the time of the survey was 5.7%. The lowest levels were found in the region of Saint-Louis (the region where Richard Toll is located), where no cases were detected, and in the regions of Dakar (0.8%) and Louga (1.4%) (DHS, 2008). This success can be attributed to the strong involvement of local institutions, who provide excellent distribution of impregnated mosquito nets during prenatal consultations for women and enable access to effective antimalarials and rapid diagnostic tests, without supply disruptions (Diop, 2012). In our study, which will take place exclusively during the dry season, we can therefore reasonably not take into account the effect of malaria on anemia.

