# 11. Biometrics and data analysis

**11.1. Results analysis plan**

A descriptive analysis will first be carried out, along with a comparison of baseline characteristics between both groups: proportion of children who are anemic, average hemoglobin levels, attrition of households etc. Covariates collected during the study at baseline (socio-economic level of the household, household composition etc.) corresponding to the two groups will be compared through univariate analysis. The efficacy of treatment will be evaluated using an adjusted multivariate analysis, adjusting using covariates that may have a confounding factor: length of participation in the study or covariates whose distribution is different between the 2 groups.

The analyses will be performed on the main response variable "proportions of households respecting the contract outlined at the beginning of the study", in terms of volume and milk collection frequency. These proportions will be compared between the two groups.

Secondary responses variables (proportion of children presenting mild, moderate or severe anemia; proportions of children with stunting, undernutrition or wasting) will be analyzed on the intent-to-treat population, gathering all the children who were attributed to a group for whom hemoglobin measurement results are available over 6 months, regardless of the group. The analysis will be adjusted for age and risk factors for anemia if their distributions are different between the two groups.

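### The lottery appears to be drawn separately on each of the four collection routes, but the stated adjustment rule leaves route out of the analysis; a prespecified route term is a free improvement

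*Protocol*

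**What the plan says.** **The draw.** Protocol Summary, 4. Trial Procedures: "An information-sharing meeting will be held on each collection route", and one task of that meeting is to "perform the intervention lottery to define the treatment and control groups". Section 10.1 also describes one meeting per route. Section 8 says "The two groups will be chosen by lottery at the first information-sharing meeting". Sections 5 and 7 make the concession the unit of randomization. No section uses the word stratification or gives an allocation ratio within a route.

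**The analysis.** Section 11.1 says of the main outcome, the proportion respecting the milk contract, only that "These proportions will be compared between the two groups". Its adjusted analysis takes length of participation or "covariates whose distribution is different between the 2 groups". Age and anemia risk factors enter the nutrition analysis on the same condition of observed difference. Section 11.2 uses difference in differences for anemia and hemoglobin, allows a propensity score if needed, and makes all tests one-sided. Route is named in none of these.

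**Why place may matter.** Section 4, Location of the study: "The herding in the Walo is of a more sedentary/agro-pastoral nature whereas the herding in the Dieri is generally pastoral with transhumance". Sections 7 and 11.3 name transhumance as a cause of non-participation and attrition.

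**The concern.** If each route has its own draw, route is part of the randomization and belongs in the analysis whatever its observed balance. The rule in 11.1 works the other way. It looks for covariates that differ between arms, and a factor balanced by separate draws will normally not differ. The better the lottery balances route, the more surely the rule drops it.

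When route predicts the outcome, separate draws with equal shares make the true variance of the treatment difference smaller than the unstratified formula assumes. The reported standard error is then too large, the test falls below its nominal level, and power is lost. The milk outcome is the most exposed, because regular supply in the dry season is what sedentary and transhumant herding would be expected to affect.

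**Working it through.** **Inputs from the protocol.** Four routes (Section 5); one-sided tests (Section 11.2); anemia 75% v 60% with 80% power and 165 children per group (Section 7). The 165 is reproduced by a two-sided 5% calculation with continuity correction. Without the correction the two-sided figure is 152; one-sided without correction it is 120. The anemia check below therefore uses both 152 (two-sided) and 120 (one-sided) as effective numbers per arm.

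**Inputs assumed.** Contract success by route is not in the documents. Three patterns over four equal routes are used, with equal allocation on each.

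**Step 1: share of variance due to route.** f = Var(p_r) / [p̄(1 − p̄)], with p̄ = 0.5:
- 35/35/65/65%: 0.0225/0.25 = 9%
- 30/30/70/70%: 0.04/0.25 = 16%
- 20/40/60/80%: 0.05/0.25 = 20%

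**Step 2: true size of the unstratified one-sided 5% test.** Φ(−1.645/√(1 − f)), with √(1 − f) = 0.954, 0.917 and 0.894.

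**Step 3: power.** Set the effect so that the unstratified formula promises 80% (1.645 + 0.842 = 2.487), then apply the true, smaller variance to both tests:
- without route: Φ(0.842/√(1 − f))
- with route: Φ(2.487/√(1 − f) − 1.645)

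| f | size without route | power without route | power with route | loss |
|---|---|---|---|---|
| 9% | 4.2% | 81.1% | 83.2% | 2.1 points |
| 16% | 3.6% | 82.1% | 85.7% | 3.6 points |
| 20% | 3.3% | 82.7% | 87.2% | 4.5 points |

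A simulation agrees (four routes, 40 concessions per arm per route, separate draws, 4,000 runs). With success of 25/25/65/65%, power for a 13-point effect was 78.1% without route and 81.9% with it, and null rejection was 3.5% and 4.8%.

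**Step 4: anemia, compared at a single time.** Power = Φ[(0.15 − z√V₀)/√V], where V is the true within-route variance and V₀ is the null variance, taken as total (without route) or within-route (with route). The SD of route prevalence is assumed.

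| SD of route prevalence | 152 per arm, two-sided: without / with route | 120 per arm, one-sided: without / with route |
|---|---|---|
| 0 | 80.0 / 80.0% | 80.1 / 80.1% |
| 0.05 | 80.2 / 80.5% | 80.3 / 80.6% |
| 0.10 | 80.6 / 81.9% | 80.7 / 81.8% |
| 0.15 | 81.4 / 84.2% | 81.5 / 83.8% |

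The loss is 0 to about 3 points.

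**Step 5: confounding by route.** It is exactly zero when the treated share is the same on every route and retention does not differ by arm. Two departures, assuming two zones of equal size with success of 65% (Walo) and 35% (Dieri) and no true effect:
- *Allocation.* If 55% of Walo and 45% of Dieri concessions are drawn to treatment, the arms show (0.55 × 65 + 0.45 × 35) − (0.45 × 65 + 0.55 × 35) = 51.5 − 48.5 = 3 points.
- *Retention.* If 10% of Dieri households are lost in one arm and 30% in the other, with none lost in the Walo, the arms show (32.5 + 15.75)/0.95 = 50.8% and (32.5 + 12.25)/0.85 = 52.6%, a gap of about 1.9 points.

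**Step 6: would the rule in 11.1 catch these?** Take 660 children at 2 per household, so 330 households and 165 per arm, and assume one household per concession. The 55% v 45% split gives z = 0.10/√(0.25 × 2/165) = 1.82, p = 0.07. The retention case leaves about 157 and 140 households, of which 52.6% and 58.8% are in the Walo, p = 0.28. A 5% screen flags neither.

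**The case against.** **Stratification is inferred.** Only the summary puts the draw at a meeting on each route. Section 10.1 lists the lottery among the terms to be explained, and Section 8 does not mention routes. This stands as a caution. The reading still fits: a second meeting follows 10 days later, so Section 8's first meeting can be the first of two rounds on each route.

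**The spread between routes is assumed.** This stands. The target is also scaled to lactating cows, which removes part of the difference in herd size, and the text does not say which route lies in which zone.

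**Model terms belong in a statistical analysis plan.** Silence alone would not be a finding. Here, though, the protocol states a selection rule, and that rule leaves out the factor by which the lottery is drawn.

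**Imbalance would be caught.** In part. The covariate list in 11.1 is open-ended and 11.2 allows a propensity score. But route is not named, the score is optional, and imbalances worth 2 to 3 points can pass a 5% screen.

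**Stronger readings that the documents do not support.**
- A reader might compare the power with route (83%, 86%, 87%) with a nominal 80%, or take 1/(1 − f) = 1.10, 1.19 and 1.25 as 10% to 25% more households for free. Both ignore that separate draws also reduce the true variance of the unadjusted comparison. The ratio 1/(1 − f) describes the reported variance, not the sample size at equal power.
- A reader might infer that every outcome is confounded by route. Balanced draws leave no allocation confounding, and difference in differences removes time-constant route effects for anemia and hemoglobin.
- A reader might cite the remark in Section 10.3 that infection risk "which may vary from one zone to the other". The protocol then sets malaria and schistosomiasis aside for this study and handles other helminths by deworming at baseline.

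**Conclusion.** The point holds as a free improvement, mainly for the milk outcome. The stated rule leaves out a factor that the lottery, on its natural reading, balances by design. The consequence is a conservative test, with no added false positives: a size of about 4.2% to 3.3% instead of 5%, and a power loss of about 2 to 4.5 points, if route explains 9% to 20% of the variance in contract success. For anemia the loss is 0 to about 3 points in a single-time comparison.

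Confounding is an alternative to this loss and not part of it. It arises only if allocation shares, or retention by arm, differ by route, and it is worth about 2 to 3 points under the assumed values. For anemia and hemoglobin only route-specific trends or differential attrition could produce it. All these sizes rest on assumed route-level rates, and the case as a whole rests on the draw being made route by route.

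**What to change.** 1. In Section 8, state that the lottery is drawn separately on each collection route, and give the allocation ratio within each route.
2. In 11.1 and 11.2, include collection route as a prespecified four-level fixed factor in every between-group analysis, whatever its observed balance.
3. For contract success, report a route-stratified (Mantel-Haenszel) or regression-standardised risk difference.
4. Cluster standard errors on the concession.

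The cost is a few sentences and 3 degrees of freedom. Households are recruited at route meetings and supply milk on those routes, so no new data are needed.

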In 2006, the Laiterie du Berger (LDB), a social venture later supported by Danone Communities, Credit Agricole, the Grameen Foundation, and other partners, started to collect milk from pastoralist households living near the town of Richard Toll in the Senegal River Valley. LDB’s business model is to produce high-quality products (primarily yogurt) for mostly urban populations, using fresh milk that it collects itself twice a day from households living within 50 km of its processing plant. Over the years, LDB has built up a reliable base of 700 milk suppliers on 4 main collection routes. At the end of the month, suppliers come to LDB and collect the payment for their month’s production. Part of these payments can be used to purchase discounted animal feeds, which appears to be an important incentive for suppliers. They may also receive an in-kind advance (in animal feeds) of up to 30% of the past month’s production, if they face specific liquidity and/or animal feed needs.

The current study aims to test a type of incentive among farmers to encourage them to provide milk to LDB more regularly during the dry season, while investigating and explaining the mechanisms involved. The incentive will be distributed as a bonus, after a contract with a target volume (corresponding to 1 liter of milk per lactating cow per day) and regularity in the frequency of milk collection has been agreed upon at the beginning of the dry season. The incentive tested will be a dairy product produced by LDB itself: fortified Thiakry. This form of incentive corresponds to the "Value Chain" concept^^[[1]](#footnote-1)^^: the initial product is the milk produced by herders and the processing of the milk produces in yogurt to which millet and fortification are added. This results in a final value-added product (fortified Thiakry) that will be made accessible to herders.

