# 2. Objectives of the study

*Overall objective:* to demonstrate the "Value Chain" concept in a contractual agreement linking the Laiterie du Berger and milk producers in the area of Richard Toll, Senegal.

*Specific objectives:* to compare the results of a micronutrient-fortified Thiakry intervention with a control group, specifically concerning:
- Increasing the volume of milk and the frequency of collection during the dry season
- Reducing the prevalence of anemia among children aged 2 to 5 years

3. Criteria for assessment

*Main outcome of the intervention:* proportion of herders who have reached their contract objective defined in the beginning of study, in terms of volume and collection frequency for milk over the duration of the study

*Main outcome for the "Nutrition" component:* proportion of children 2 to 5 years presentingsevere, moderate, and mild anemia (defined thresholds respectively are <7, between 7 and 9.9, and between 10 and 10.9 g/dl of hemoglobin).

*Secondary outcome of the "Nutrition" component (at 6 and 12 months of follow-up):*- Mean level of hemoglobin (in g/dl)
- Proportion of children 2 to 5 suffering from stunting (Height-for-Age Indices <-2SD)
- Proportion of children 2 to 5 years suffering from acute malnutrition (Weight-for-Height Indices <-2 SD)
- Proportion of children 2 to 5 years who are underweight (Weight-for-Age Indices <-2 SD)

- Household food consumption

- Children’s dietary diversity

*Definitions:*

- Mild anemia in children: level of hemoglobin between 10 and 10.9 g/dl of blood

- Moderate anemia in children: level of hemoglobin between 7 and 9.9 g/dl of blood

- Severe anemia in children: level of hemoglobin less than 7 g/dl of blood

- Stunting (Height-for-Age Indices <-2SD)

- Acute malnutrition or wasting (Weight-for-Height Indices <-2 SD)

- Underweight (Weight-for-Age Indices <-2 SD)

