**11.2. Methods and data analysis models**

The impact of the intervention will be analyzed using the "difference in differences" method: the difference in the prevalence of anemia for children 2 to 5 years or the difference of average hemoglobin levels, i) between the treatment and the control group and ii) between the beginning and the end of the intervention. It will be possible to use a propensity score, determined from the baseline characteristics, in order to check the comparability between groups and, if necessary, to use the score as an adjustment factor. All tests performed will be unilateral, with a 95% confidence interval. The analysis will be performed using STATA 12.0 (Stata statistical software, Stata Corporation, College Station, Texas USA).

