**12.4. Information sharing, archiving, and document storage at the end of the study**

The partners have agreed not to share the raw data present in the databases. In particular:
- Trade secrets of LDB (preparation of recipes including Thiakry) cannot be shared. Only fortification levels and associated molecules may be detailed in research publications.
- Data collected daily by LDB will not be used for publications that will be made public within 6 months after the data’s collection.

- Data from household surveys conducted by IFPRI, GRET, and PPZS will not be disseminated in raw format without the agreement of the institution who collected them. In all cases, the last names, first names, geographical coordinates, and all other identifying information cannot be diffused to third parties.

- The source of all data should be clearly mentioned during oral communications (presentations) or written communications (publications).

The principal investigators and the coordinating center will archive and keep documents related to the study for a period of at least 30 years. These documents will include the protocol of the study and the informed consent of mothers, as well as any administrative documents.

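### Adjustment of the main milk outcome depends on observed imbalance, and no pre-study milk delivery is named as a covariate, so available precision is not secured

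*Protocol*

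**What the plan says.** The main outcome of the intervention is the "proportion of herders who have reached their contract objective defined in the beginning of study", judged on volume and collection frequency (criteria for assessment, following Section 2). Section 11.1 names this as the main response variable and says: "These proportions will be compared between the two groups".

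The paragraph before that is general: "The efficacy of treatment will be evaluated using an adjusted multivariate analysis". Its covariates are "length of participation in the study or covariates whose distribution is different between the 2 groups". Section 11.2 adds an option: "It will be possible to use a propensity score, determined from the baseline characteristics", to check comparability and, if needed, to adjust.

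Section 11.2 also sets out difference in differences, but spells it out only as "the difference in the prevalence of anemia for children 2 to 5 years or the difference of average hemoglobin levels". Milk is not mentioned there. The baseline questionnaire in Section 10.3 lists herd data such as herd size, but not past milk delivery.

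On the dairy's records, Section 1 says: "At the end of the month, suppliers come to LDB and collect the payment for their month’s production". It adds that in-kind advances can reach 30% of the past month's production. Section 12.4 shows that daily data are also gathered: "Data collected daily by LDB will not be used for publications that will be made public within 6 months after the data’s collection".

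**The concern.** In a randomised trial, a baseline difference between arms is a chance event. The main reason to adjust is that a covariate predicts the outcome, and a predictive covariate reduces variance even when it is perfectly balanced. The rule in Section 11.1 selects on the wrong property: a strongly prognostic but balanced covariate stays out, and a weakly prognostic but imbalanced one goes in. It also leaves the form of the main model undecided until the data have been seen.

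Past delivery is the natural prognostic covariate here, because litres and regularity are the two dimensions of the contract. Under the stated rule it could enter only if someone obtained it and then found it imbalanced. At stake is a wider interval and a greater chance of missing a real effect on the trial's main question.

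The only covariate admitted regardless of balance, length of participation, is measured after randomisation and so cannot serve as a baseline.

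**Working it through.** **What the text allows**

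| Place | Can pre-study delivery enter the milk analysis? |
|---|---|
| 10.3 baseline questionnaire | Not listed |
| 11.1 adjusted analysis | Only if obtained and found to differ between arms |
| 11.2 propensity score | Optional, tied to comparability |
| 11.2 difference in differences | Spelled out for anemia and hemoglobin only |

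No route secures it in advance.

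**Illustrative size**

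The protocol gives no milk success rate, target difference or correlation, and its only sample-size calculation (Section 7) concerns anemia. There is therefore no milk figure to reproduce.

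From the protocol: 700 families (Summary) and one-sided tests (11.2), taken at the 5% level of Section 7.

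Assumed: an equal split, so 350 per arm; one contract result per family; success of 50% against 60%; correlation ρ between past delivery and contract success (yes or no) of 0.3 to 0.5; no clustering.

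Unadjusted SE = √[(0.5×0.5 + 0.6×0.4)/350] = √(0.49/350) = 0.0374.

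Adjusted SE = 0.0374 × √(1 − ρ²).

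Power = Φ(0.10/SE − 1.645).

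| ρ | √(1 − ρ²) | SE | 0.10/SE | Power |
|---|---|---|---|---|
| 0 (unadjusted) | 1 | 0.0374 | 2.673 | 84.8% |
| 0.3 | 0.954 | 0.0357 | 2.802 | 87.6% |
| 0.4 | 0.917 | 0.0343 | 2.916 | 89.8% |
| 0.5 | 0.866 | 0.0324 | 3.086 | 92.5% |

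The gain is about 3, 5 and 8 percentage points, and the interval is about 5%, 8% and 13% narrower.

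**Simulation check**

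With 700 households, 50% against 60% and 3,000 runs, a linear model with robust standard errors was fitted. The covariate was correlated 0.3, 0.5 or 0.7 with a continuous trait underlying success. Power rose from about 84–85% to 86%, 89% and 94%. Those trait correlations are smaller on the ρ scale above: 0.5 gives R² = 0.157 with the yes/no outcome, so ρ = √0.157 ≈ 0.40. The simulated 89% agrees closely with the 89.8% in the table.

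**Clustering**

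Concessions are randomised, so success may cluster. With an illustrative design effect of 1.3, the unadjusted SE is 0.0374 × √1.3 = 0.0427 and power is 75.8%. At ρ = 0.5, SE is 0.0427 × 0.866 = 0.0369 and power is 85.6%. Clustering lowers both figures and leaves room for a larger gain.

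**The case against.** - **The comparison is not stated to be unadjusted.** A reader might infer from the sentence on proportions that raw proportions are the whole analysis. The documents do not support that: the adjusted analysis in the preceding paragraph is not limited to nutrition, and 11.2 allows a propensity score. This objection stands. The defect is the selection rule, not an absence of adjustment.
- **Covariate lists belong in the SAP.** Not naming past delivery would not by itself be a finding. But the protocol does fix a rule for choosing covariates, and that rule can be criticised as written.
- **The records may not be in hand or separable.** A reader might assume that the study already holds each herder's history. Section 12.1 says only that a data-sharing agreement will be signed, and does not mention pre-study records. Section 12.4 restricts publication of daily data and gives neither unit nor period. Section 5 puts about two households on a container, and 10.4 refers to the herder responsible for it. What stands is that monthly production by supplier is evidently recorded; pre-study delivery frequency is not documented for any unit. A coarser record lowers ρ but remains a valid baseline.
- **The correlation may be low.** The target is scaled to lactating cows, so plain litres partly measure herd size, which the target removes. Dry-season delivery drops and becomes irregular, so earlier months may predict it poorly. Both points are fair, and the documents do not settle where in the range ρ falls.

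**Conclusion.** The point holds as a matter of efficiency. Section 11.1 ties adjustment to observed imbalance, and no pre-study milk value is named for the main outcome despite evidence that suppliers' production is recorded. The expected precision of a prognostic baseline is therefore left to chance.

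A reader might infer bias. Omitting a pre-randomisation covariate does not bias a randomised comparison. That statement covers past delivery only and does not vouch for adjusting on length of participation. Nor do the documents support any fixed power loss. The gain of about 3 to 8 points at one-sided 5% rests on the assumed 350 per arm, 50% against 60%, ρ of 0.3 to 0.5 and no clustering. A gain of 5 points needs ρ of about 0.4. The absence of a power calculation for milk is a separate matter and does not make this one more serious.

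**What to change.** In Section 11.1, specify for the main outcome a model of contract success on arm that always adjusts, whatever the observed balance, for:

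- dairy delivery before the lottery, in litres and, where recorded, delivery frequency, at the supplier or container level at which records exist;
- collection route.

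Litres are best expressed per lactating cow, because the target is scaled that way. The cow count should predate the lottery: by Section 10.1 contract targets are set at the second meeting, after the draw, so a count fixed there is not strictly baseline.

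Use standard errors clustered by concession, report the standardised risk difference, and include a missing-record indicator for suppliers without a history. Keep the unadjusted proportions as a supporting result.

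The cost is a short addition to 11.1 and an extract of dairy records, which the planned agreement in 12.1 should explicitly cover. No visits or participants are added. The downside is the work of obtaining and linking the records, and that some suppliers will have no history.

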Different targeted interventions to provide iron supplements to vulnerable populations have been evaluated (Berger, 2002). Approaches based on increased consumption of iron and food diversity are important strategies for the prevention of iron deficiency and iron-deficiency anemia in the general population. However, integrated approaches that combine supplementation interventions in iron and other health measures (such as deworming, actions to combat malaria, mass treatment for schistosomiasis) were necessary in areas where iron deficiency was not the only cause of anemia. Education and respect for good dietary practices are also essential (Buttha, 2008). Finally, the implementation of interventions in the fight against micronutrient deficiencies (through supplementation, fortification, and dietary modification) should be integrated in agriculture, welfare, and/or health programs (Olney, 2012).

Senegal has seen significant progress in combating malnutrition over the past two decades. Alleviating child malnutrition has been high on the Senegalese policy agenda, with a dedicated unit – the Cellule contre La Malnutrition (CLM) – coordinating major activities in-country and reporting directly to the prime ministers’ office. According to the 2011 DHS report, 83% of children under 5 years and 54% of mothers are anemic in Senegal. According to the same report, growth delays (indicator of chronic malnutrition) affect 27% of children, with thinness or wasting (acute malnutrition indicator) affecting 10% of children and 18% being underweight (DHS 2011).

According to a 2012 report of CLM on the iron status of children aged 12-59 months across Senegal, the prevalence of anemia is 83% for children 12-23 months and declines to 49% for children 48-59 months (MI, 2012). Analyses on iron status indicate that 64.5% of children have an iron deficiency, ranging from 64.3% for children 12-24 months and decreasing to 42.5% for children 48-59 months. Finally, according to the latest Smart 2012 survey, conducted by CLM in the department of Dagana among children 6-59 months, acute malnutrition affected 11.4% of children (as compared to 8.80% nationally), stunting impacted 13.6% (compared to 15.50% nationally), and 15.5% were underweight (compared to 14.50% nationally) (CLM, 2012).

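### Growth is analysed only as three proportions below -2 SD; the mean z-scores, which must be computed anyway, should be added as analysed secondary outcomes

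*Protocol*

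**What the plan says.** Section 3 of the protocol (criteria for assessment) lists three growth outcomes at 6 and 12 months, each a proportion below a cut. The first is "Proportion of children 2 to 5 suffering from stunting (Height-for-Age Indices <-2SD". The other two have the same form: wasting is the share with a weight-for-height index under the same limit, and underweight the share with a weight-for-age index under it. The Summary repeats this list.

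Section 11.1 names the growth variables for analysis as "proportions of children with stunting, undernutrition or wasting"; I read its middle term as the underweight outcome of section 3. No mean height-for-age, weight-for-height or weight-for-age index appears as an outcome or analysis variable anywhere in the protocol.

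Hemoglobin is handled differently. Besides the anemia proportions, section 3 lists "Mean level of hemoglobin (in g/dl" as a secondary outcome, and section 11.2 applies the difference-in-differences analysis to both anemia prevalence and average hemoglobin.

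Section 1 gives survey prevalences for the department where the trial takes place, among them "stunting impacted 13.6% (compared to 15.50% nationally". In the same survey, wasting stands at 11.4% and underweight at 15.5%. Section 7 sizes the trial on anemia alone. No growth effect or growth power is stated.

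**The concern.** A child cannot be placed below -2 SD without first having a z-score, so the continuous values will be in the data file. Reducing each to yes or no discards how far a child lies from the cut. The loss grows as the cut moves into the tail, and at prevalences of 11-16% it lies well into the tail.

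The trial was sized for an outcome near 75%, so nothing in the design protects comparisons of outcomes this rare. A general improvement in growth could leave all three proportions non-significant and then be read as no effect on growth. Switching to means after seeing that result would be a post hoc choice. The protocol keeps both forms for hemoglobin and gives no reason for treating growth otherwise.

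**Working it through.** **Inputs.** Section 1 gives prevalences p for Dagana, ages 6-59 months: wasting 0.114, stunting 0.136, underweight 0.155. It also gives national figures from the same survey (0.088, 0.155, 0.145) and from the 2011 DHS (0.10, 0.27, 0.18). Sections 7 and 11.2 give a one-sided test at 5%. Section 7 gives 165 children per group before clustering.

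**The plan's own figure.** There is none for growth. For anemia, the clustering step reproduces: 330 × (1 + (2 - 1) × 0.3) = 429, stated as 430. So 215 enrolled per group correspond to 215/1.3 ≈ 165 effective children. I take 165 as given. It matches a two-sided, continuity-corrected calculation rather than the stated one-sided one (which gives 120, or 133 with correction), but that does not affect this point.

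**Step 1: information kept by the cut.** For normal z-scores and a small shift common to all children, the efficiency of the proportion relative to the mean is φ(z)²/[p(1-p)], with z = Φ⁻¹(p).

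| Outcome (Dagana) | z | φ(z) | p(1-p) | Efficiency | Inverse |
|---|---|---|---|---|---|
| Wasting | -1.206 | 0.193 | 0.101 | 0.37 | 2.71 |
| Stunting | -1.099 | 0.218 | 0.118 | 0.41 | 2.47 |
| Underweight | -1.015 | 0.238 | 0.131 | 0.43 | 2.31 |

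The proportions therefore need about 2.3 to 2.7 times as many children. The national figures give 0.32, 0.43 and 0.42; the DHS figures give 0.34, 0.55 and 0.47. The full range is 0.32-0.55.

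**Step 2: power for assumed shifts s (in SD).** Let p₁ = Φ(z - s).

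- Proportions: Φ{(p - p₁)/√[(p(1-p) + p₁(1-p₁))/165] - 1.645}
- Means: Φ{s√(165/2) - 1.645}

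Example, stunting with s = 0.3: p₁ = 0.081, difference 0.055, standard error 0.0341, ratio 1.613, power Φ(-0.032) = 49%. For the mean: 0.3 × 9.083 = 2.725, power Φ(1.080) = 86%.

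| Shift | Wasting | Stunting | Underweight | Mean z-score |
|---|---|---|---|---|
| 0.1 SD | 13% | 14% | 14% | 23% |
| 0.2 SD | 28% | 29% | 31% | 57% |
| 0.3 SD | 45% | 49% | 51% | 86% |
| 0.4 SD | 63% | 67% | 70% | 98% |

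**Step 3: benefit confined to undernourished children.** Take an index with SD 1 and mean -2 - z, and let only children below -1 SD gain 0.3. Every child who crosses -2 was below -1, so power on the proportions stays at 45-51%. The share who gain is Φ(1 + z) = 0.42, 0.46 and 0.49 for wasting, stunting and underweight, so the mean rises by only 0.126, 0.138 and 0.148. The SD in the treated group falls to about 0.89. For wasting, 0.126/√[(1 + 0.887²)/165] = 1.21 and power is Φ(1.21 - 1.645) = 33%; for stunting it is 38% and for underweight 41%. If only children below -1.5 SD gain, power on the means falls to 17-22%. Here the proportions are the better test.

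**The case against.** **These are secondary outcomes.** The specific objectives are milk supply and child anemia, and the trial was never sized for growth. That stands and limits the weight of the point.

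**A statistical analysis plan could add means.** The parenthesis in section 11.1 also omits mean hemoglobin, which section 11.2 analyses, so it is not exhaustive. But mean hemoglobin is in the outcome list and mean z-scores are nowhere. The protocol fixes growth as proportions in the Summary, in section 3 and in section 11.1.

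**The advantage of the means depends on the effect pattern and size.** This stands. At 0.1 SD the gain is only 9-10 points and both analyses are weak. If the benefit falls on the most undernourished children, the ranking reverses (step 3).

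A reader might infer two stronger conclusions, and neither is supported:

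- *That means should replace the proportions, leaving those descriptive.* Step 3 shows this could lower power, and the hemoglobin and anemia pair keeps both forms as analysed quantities.
- *That the proportions will probably be non-significant whatever the product does.* At a 0.4 SD shift their one-sided power is 63-70%.

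**Conclusion.** The point holds as a loss of sensitivity on secondary outcomes. With roughly normal z-scores and a similar shift in all children, the planned growth proportions keep about 37-43% of the information at the Dagana rates, and 32-55% across all rates the protocol quotes. Over assumed shifts of 0.2 to 0.4 SD, adding the means offers one-sided power of 57-98% where the proportions offer 28-70%.

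This rests on four assumptions: effect sizes that the protocol does not state; rates for ages 6-59 months applied to ages 2-5; the anemia intracluster correlation carried over to growth to reach 165 effective children; and a comparison at one time point. Clustering and the difference-in-differences analysis change absolute power, and the ratio only approximately. Because a benefit confined to the most undernourished favours the proportions, the documents support analysing both forms, not choosing one. The main milk-supply and anemia results are untouched.

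**What to change.** In sections 3 and 11.1 (and the matching list in the Summary), add mean height-for-age, weight-for-height and weight-for-age z-scores as analysed secondary growth outcomes at 6 and 12 months. Keep the three proportions below -2 SD as analysed outcomes beside them, as is done for mean hemoglobin and anemia.

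The cost is a few words and three more model fits at each time point. No children or measurements are needed beyond those the proportions already require. The one downside is small: three more secondary comparisons at each time point, to be read as secondary.
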